## Efficacy: secondary analysis

All the secondary statistical analysis will be detailed in the statistical analysis plan (SAP).

## Safety and Tolerability

All randomised patients who have taken at least one dose of the study medications will be considered for the following analysis.

All Adverse Events (AEs) will be tabulated according to degree of seriousness, time of treatment at AE onset, severity, relation to study drug, action taken, if any, and final outcome.

Vitals signs and ECG will be analysed descriptively.

ECG results will be classified as normal and abnormal. The evaluation of ECG and QT interval will be done according to the EMEA directive “point to consider: the assessment of the potential for QT interval prolongation by non-cardiovascular medicinal products”. EMEA (CPMP), London 17/12/1997 (CPMP/986/96).

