## Secondary Objectives

The secondary objectives of the study will be the between treatment comparison of:

- the uncorrected Day 28 cure rates of both drugs (risk for rescue therapy);

- the safety profiles of the two treatments;

- times of parasite clearance (PCT);

- time of fever clearance (FCT);

- gametocyte prevalences and densities on days 7, 14, 28, 42;

- haematological recovery (Haemoglobin (Hb) changes from day 0 to day 28 and day 42;

- cure rates at D42 (PCR corrected and PCR uncorrected).

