## Rescue Treatments

Patients with clinical treatment failure will be withdrawn from the study, treated, and followed up as per local practice. They will not have study investigations performed thereafter. Patients requiring rescue therapy (ETF, LCF) will be treated by members of the study team with quinine 10 mg/kg orally three times a day for 7 days or any other appropriate oral treatment unrelated to the study drugs. Any patient, who is diagnosed with severe malaria or danger signs during follow-up, will be referred for treatment with parenteral quinine and supportive measures at the local facility or hospital.

Patients with asymptomatic recurrent parasitaemia will also receive rescue therapy.

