# PATIENT WITHDRAWAL CRITERIA

During the study, the following conditions are reasons **for stopping the study treatment and/or for excluding the patients from further efficacy assessments:**

1. Any treatment failure (including early failures);

2. Withdrawal of informed consent;

3. Use of antimalarial drugs (or antibiotics with antimalarial activity) outside of the study protocol;

4. Persistent vomiting of study drugs **on Day 0**  (at least twice the same dose);

5. Failure to complete the study treatment

6. Investigator's request for safety reasons (for example, onset of serious adverse events, necessitating study interruption);

6. Lost to follow-up (unable to locate the patient) before Day 28.

Patients with one or more of the conditions listed above will have to be followed-up for the safety assessment until Day 42

These reasons for premature withdrawing will be referred to Day 28 (primary evaluation time).

The reasons for withdrawing between Day 29 and Day 42 will also be recorded in the study CRF.

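### Section 9.4 tabulates all adverse events with no split at recurrence or rescue, and sections 4.4 and 5 disagree on whether clinical failures are followed for safety afterwards

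*Combined protocol and SAP*

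**What the plan says.** Section 9.4 defines the safety population: "All randomised patients who have taken at least one dose of the study medications will be considered for the following analysis". It then says: "All Adverse Events (AEs) will be tabulated according to degree of seriousness, time of treatment at AE onset, severity"; the full list of factors after seriousness is "time of treatment at AE onset, severity, relation to study drug, action taken, if any, and final outcome". Recurrence and rescue are not among them. Vital signs and ECG are to be described, with ECGs classed as normal or abnormal.

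Section 4.4 provides rescue for early treatment failure and late clinical failure as "quinine 10 mg/kg orally three times a day for 7 days or any other appropriate oral treatment unrelated to the study drugs". It then extends rescue to asymptomatic recurrent parasitaemia, without waiting for PCR or distinguishing recrudescence from new infection.

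Two statements govern what happens next. Section 5, whose first listed reason is any treatment failure, says: "Patients with one or more of the conditions listed above will have to be followed-up for the safety assessment until Day 42". Section 4.4 says: "Patients with clinical treatment failure will be withdrawn from the study, treated, and followed up as per local practice", and adds: "They will not have study investigations performed thereafter".

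Section 2.2 lists the safety profiles as a between-treatment comparison. The same list describes the uncorrected Day 28 cure rate as the risk of rescue and compares that between arms too. Section 7.1.4 counts any new or worsening event as an adverse event, with no exception for a recurrent episode or for events after rescue.

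**The concern.** A child who is rescued has a second malaria episode and takes a drug that is not the study drug. Events from either are adverse events under section 7.1.4 and, if collected, enter the same table as events from the first treatment course. How many there are depends on how many children in the arm are rescued, which the protocol itself treats as an outcome that may differ between arms. The arm with more recurrences could then look less well tolerated for reasons unrelated to the tolerability of its study drug.

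If clinical failures instead leave all study follow-up, as section 4.4 can be read, the arm with more of them is observed for less time and contributes fewer late events. The distortion could then run the other way.

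This matters because safety is a named comparison, and because section 3.4.1 justifies the 2:1 allocation partly by the size of the DHA+PPQ safety database.

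**Working it through.** **The plan's own figures.** The documents give no figure for the safety comparison. The nearest stated figures are the powers for non-inferiority in section 3.4.1. With power = Φ((0.05 − c)/SE − 1.96) and c = (1/nT + 1/nC)/2:
- Modified ITT, 900/450 at 91%: SE = √(0.91 × 0.09 × (1/900 + 1/450)) = 0.0165, c = 0.0017, power 83.3% (stated: 83%).
- Per Protocol, 700/350 at 93%: SE = 0.0167, c = 0.0021, power 81.7% (stated: 82%).

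Both reproduce, and a split of the safety tables changes neither.

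**Do the design assumptions imply unequal rescue?** No. Section 3.4.1 gives one cure rate per population (91% or 93%) with no arm difference. Those rates are PCR-corrected, however. Rescue follows the uncorrected failures, which include new infections, and no uncorrected rate is given. Unequal rescue is therefore neither implied nor excluded.

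**Illustration 1 (all rates assumed).** A share a of rescued children has an adverse event they would not otherwise have had. Gap = a × (difference in rescue proportion).

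| Rescue in the two arms | a = 0.2 | a = 0.4 |
|---|---|---|
| 20% vs 10% | 0.2 × 0.10 = 2 points | 0.4 × 0.10 = 4 points |
| 30% vs 15% | 0.2 × 0.15 = 3 points | 0.4 × 0.15 = 6 points |

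As a yardstick, at an assumed 30% incidence and 1000/500 children, SE = √(0.3 × 0.7 × (1/1000 + 1/500)) = 2.5 points and 1.96 SE = 4.9 points. Only the 6-point case exceeds it.

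**Illustration 2 (all rates assumed).** In each arm 10% have an event before rescue, a proportion r is rescued, and a share q of rescued children without an earlier event has one afterwards. Proportion with an event = 0.10 + 0.90 × r × q. Differences are DHA+PPQ minus A+L, with the higher rescue rate placed in the A+L arm for illustration only.

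| Rescue (1000 / 500) | q = 0.2 | q = 0.5 | q = 0.8 |
|---|---|---|---|
| 10% / 10% | 0 | 0 | 0 |
| 10% / 20% | −1.8 (z −0.98) | −4.5 (z −2.17) | −7.2 (z −3.18) |
| 10% / 30% | −3.6 (z −1.89) | −9.0 (z −4.09) | −14.4 (z −6.01) |

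Example, 10% / 20% with q = 0.5: 0.145 against 0.190; SE = √(0.145 × 0.855/1000 + 0.190 × 0.810/500) = 0.0208; z = −0.045/0.0208 = −2.17. Counting only events before rescue, the difference is zero in every cell, because 10% was assumed in both arms.

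**Do the listed factors already separate rescue?** Time of treatment at onset is not defined. Section 3.8 heads the visits up to Day 28 as the open-label treatment period, although dosing ends on Day 2, so the factor need not mark rescue. Relation to study drug is graded by investigators in an open-label trial; it informs individual cases but is not a split at a date.

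**What is collected late?** By the follow-up chart in section 3.6, routine ECGs fall on Days 0, 2 and 7. The Day 28 ECG is done only if Day 7 was abnormal, and the Day 42 ECG only if Day 28 was abnormal. A further ECG and haematology are due on the day of any recurrent parasitaemia. Late ECGs therefore come mainly from children with a recurrence or an earlier abnormality, and an arm with more recurrences has more of them, taken during a malaria episode.

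**The case against.** The strongest counter-argument is that retention to Day 42 is not settled. A reader might infer from section 5 that all rescued children certainly stay in the safety tables. Section 4.4 does not allow that inference for clinical failures. Section 9.2.1 adds that re-infected children are terminated on that day, without saying whether safety follow-up ends too. This stands: for some children the problem may be missing data, and the contradiction is part of the point. It does not supply a rule for section 9.4 under either reading.

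A reader might also infer that ECG effects of the rescue drug would accumulate in one arm. The ECG schedule makes such effects largely unobservable. What remains is the mixing of recurrence-day recordings with scheduled ones.

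Nor can it be said that causality grading leaves laboratory findings untouched. Sections 7.2 and 7.3 turn clinically important laboratory and vital-sign values into adverse events, and section 7.1.2 asks the assessor to weigh other therapy and clinical state. That helps case by case, within the limits of open-label judgement.

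Three further objections hold in part. Section 9.4 plans description, not testing, so the z values above are only a yardstick. It does not say how tables are grouped; grouping by arm is inferred from section 2.2. Section 9 defers detail to an SAP, and the text available contains no separate SAP, so the split may be intended. That makes this a request for SAP wording rather than proof of an omission.

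Finally, all events to Day 42 is a legitimate main view. A rescue-censored table should not replace it, because follow-up would then depend on outcome.

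**Conclusion.** The point holds in a limited form. Nothing in the text separates adverse events at recurrence or rescue, while sections 4.4 and 5 together allow such events to be collected and section 9.4 tabulates them all. If rescue rates differ, the safety comparison is harder to interpret.

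The size is not known. Under the assumed inputs it runs from 0 (equal rescue) to about 14 points at the extreme; at 10% against 20% rescue it is 1.8 to 7.2 points. The documents do not say which arm would have more rescue, so no direction of bias against either drug can be claimed. A reader might infer that the planned safety comparison is invalid; the documents do not support that either, since the distortion needs unequal rescue and the Day 42 table remains a proper description.

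The contradiction between sections 4.4 and 5 needs no assumption and must be reconciled. The added tables are a cheap improvement in interpretation.

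**What to change.** 1. Reconcile sections 4.4 and 5 (and the termination wording in 9.2.1), so that it is clear which safety data exist after failure, re-infection and rescue, and state in the SAP whether adverse events after rescue are collected.
2. Keep the all-event table to Day 42.
3. Define a split date for each child: the earlier of the day recurrent parasitaemia is detected (or treatment failure is declared) and the first dose of any non-study antimalarial. Add by arm (a) events with onset before that date, with person-time at risk, and (b) events with onset on or after it.
4. Summarise ECGs and haematology taken on the day of recurrence separately from the scheduled ones.

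**Cost.** One derived date and one more table set. Adverse-event onset (section 7.1.4), smear dates (section 3.6) and concomitant-treatment timing (section 4.2) are already to be recorded. Sample size, power and alpha do not change.

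**Limits.** Late reactions to study drug in rescued children fall in table (b). Symptoms that precede detection of a recurrence stay in table (a). If events cluster early, person-time rates in (a) are raised in the arm that loses more late follow-up. Table (a) should therefore be read beside the full table, not in place of it.

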# MONITORING AND QUALITY ASSURANCE

The task of the Monitor is to verify the best conduct of the study through frequent contacts by phone and in person with the Principal Investigator and site staff, in accordance with the Standard Operating Procedures and Good Clinical Practice, with the purposes of facilitating the work and attaining the objectives of the study. These visits will enable the Monitor to maintain current, personal knowledge of the study through review of the records, comparison with source documents, observation and discussion of the conduct of the study with the Investigator.

The Investigator by signing this protocol declares that he/she will permit trial-related monitoring, audits, Independent Ethic Committee review, and regulatory inspections, providing direct access to source data/documents.

The Investigator agrees to conduct the present study in full agreement with the principles of the “Declaration of Helsinki” and subsequent relevant amendments (see Appendix III).

# DATA MANAGEMENT

All data management procedures will be detailed in separate, specifically identified files that collectively will be referenced as the Data Management Plan (DMP).

Appropriate CRFs will be prepared for collection of data requested by the protocol. All response variables will be entered into an electronic database maintained by MDS Pharma services. This database will be compiled and reviewed for accuracy in accordance with MDS Pharma services internal Standard Operating Procedures concerning data management and data quality control. All data will be tabulated to generate data listings for the final report.

These data will be then exported for the creation of Statistical Analysis System (SAS) datasets that comprise the SAS database. Edit and consistency checks will also be performed as outlined in the DMP. Once all questions have been resolved, the database will be locked. The locked SAS database will be used to generate the subject listings, tabulations, and analyses.

# INVESTIGATOR RESPONSIBILITY

Except where the Principal Investigator's signature is specifically required, it is understood that the term "Investigator" as used in this protocol and on the CRFs refers to the Principal Investigator or a member of the staff that the Investigator designates to perform a certain duty under this protocol. The Investigator is ultimately responsible for the conduct of all aspects of the study.

For all other relevant Investigator responsibilities see “CPMP/ICH/135/95 Topic E6 - Guideline for Good Clinical Practice”, Chapter 4.

# TRIAL REPORTS

## Statistical Report

The Statistical Report will be prepared by the Biostatistics and Data Management Department of MDS Pharma Services after having received all the validated CRFs.

## Final Clinical Report

The Final Clinical Report will be written by MDS Pharma Services. It is structured as an Integrated Clinical Report containing clinical comments based on the data generated by the Statistical Report.

# ADMINISTRATIVE PROCEDURES

## Regulatory Authorities and Ethical Review Committee

This study will be reported to the respective National Health Authority.

The clinical protocol will be submitted for approval to the relevant Independent Ethic Committee (IEC) or Institutional Review Board (IRB) before patients can be enrolled.

Copy of the IEC/IRB approval will be transmitted from the Investigator to the Sponsor before starting the study.

## Informed Consent

All interviews will be conducted in the native language of the patients by the study personnel. Consent forms will be provided to the parents or guardians for their review (see Appendix IV). The parents or guardians will be asked to sign consent to participate in a research study. The informed consent will describe the purpose of the study, the procedures to be followed, and the risks and benefits of participation. If a parent or guardian is unable to read or write, a signature from a witness to the informed consent discussion will be obtained. Parents or guardians will be informed that participation in the study is completely voluntary and that they may withdraw their child from the study at any time without any negative consequences.

## Confidentiality and Publication of Results

All study documents are provided by the Sponsor in confidence to the investigators and his/her appointed staff. None of this material may be disclosed to any part not directly involved in the study without written permission from Sigma-Tau i.f.r. S.p.A., Pomezia (Rome) – Italy.

Presentation and publication of the study results will be carried out by Investigators jointly with the Sponsor (i.e.: Sigma-Tau), that will be informed at least 3 months before disclosure of the data, in order to discuss the content of the presentation or manuscript.

## Protocol Amendments

Once the final clinical protocol has been issued and signed by the Investigator and the authorised signatories, it must not be informally altered. Clinical protocol amendments are alterations to a legal document (the clinical protocol) and have the same legal status and must pass through the appropriate steps before being implemented. In general, any change must be approved by the IEC prior to be effective. Administrative changes need only notification to the IEC without approval.

Any subsequent amendments must be made on separate sheet and must pass through the approval process. It must be clear to the Investigator that he can not change the clinical protocol without prior discussion with Sponsor, which should give its approval.

# Study Committees

## Steering Committee

The Steering Committee (SC) comprises at least one investigator from each participating region and will assess the progress of the trial. The members of the SC will address policy and operational issues related to the protocol. The SC has responsibility for protecting the scientific conduct and integrity of the trial. Its functions include:

- Review of the protocol before ethic committee approval,
- Formulation of recommendation for any change in the design and operations of the trial during the course of the trial, when needed,
- Exclusion of patients from the per protocol analysis.

The members of the Steering Committee will be specified in the Terms of Agreement document that will be prepared no later than the first face-to-face meeting of this Committee

## Data Monitoring Board

The Data Monitoring Board (DMB) will be composed of one statistician and two or three clinicians, all of them independent from the Sponsor and its Designee. At least one of the clinicians will have experience in treating patients with the disease under study and at least one will be a malaria expert.

The main roles of the DMB will be:

 performing the interim analysis for sample size re-assessment;

 monitoring all safety data recorded while the study is ongoing;

 revising in blind a significant percentage (to be defined in the SAP) of the primary efficacy data.

The members of the DMB will be identified prior to enrolling the first patient.

**15.3 Clinical Development Committee**

The Clinical Development Committee will be responsible for:

- evaluating the recommendations of both the Data Monitoring Committee and the study Steering Committee and, if deemed appropriate, transforming them in operational decisions;
- protecting the scientific conduct, the ethical integrity, and the regulatory acceptability of the Artekin project;
- harmonizing all the studies of the Artekin project;
- addressing policies and operational issues that can impact the Artekin project.

The members appointed to this Committee will be specified in the Terms of Agreement document that will be prepared no later than the first face-to-face meeting of this Committee

# APPENDICES

**APPENDIX I**

Guidelines for Grading Patient Symptoms, signs and laboratory findings.

Table A. Guidelines for Grading Patient Symptoms.

|  | **Grade 1**  **MILD** | **Grade 2**  **MODERATE** | **Grade 3**  **SEVERE** | **Grade 4**  **LIFE THREATENING** |
| --- | --- | --- | --- | --- |
| **Subjective fever in the past 24 h** | N/A | Present (Yes) | N/A | N/A |
| ***Weakness*** | Mild decrease in activity; For children – weak, but still playing | Moderate decrease in activity; For children – weak, and playing limited | Not participating in usual activities; For children – not playing | Prostration |
| **Muscle and/or joint aches*** | Mild and/or localized complaints | Diffuse complaints | Objective weakness; function limited | N/A |
| **Headache*** | Mild, no treatment required | Transient, moderate; treatment required | Severe, constant; requires narcotic therapy | Intractable; requires repeated narcotic therapy |
| **Anorexia** | Decreased appetite, but still taking solid food | Decreased appetite, avoiding solid food but taking liquids | Appetite very decreased; Refusing to breast feed, no solids or liquids taken (< 2 years < 12 hr; > 2 years < 24 hr) | Appetite very decreased; Refusing to breast feed, no solids or liquids taken (< 2 years > 12 hr; > 2 years > 24 hr) |
| **Nausea*** | Mild, transient feeling of impending vomiting; maintains reasonable intake | Moderate and/or constant feeling of impending vomiting; intake decreased | Severe, constant feeling of impending emesis; intake decreased significantly | N/A |
| **Vomiting** | 1 episode per day | 2-3 episodes per day | Orthostatic hypotension or IV fluids required | Hypotensive shock or physiological consequences requiring IV fluid therapy |
| **Abdominal pain*** | Mild (1-3 on a scale of 1 to 10) | Moderate (4-6 on a scale of 1 to 10) | Moderate to severe (> 7 on a scale of 1 to 10) | Severe – hospitalization for treatment |
| **Diarrhea** | Transient 3-4 loose stools/day | 5-7 loose stools/day | Orthostatic hypotension or > 7 loose stools/day or IV fluids required | Hypotensive shock or physiological consequences requiring IV fluid therapy |
| **Cough** | Transient / intermittent | Persistent / constant | Uncontrolled | Cyanosis, stridor, severe shortness of breath |
| **Pruritis** | Transient pruritis | Pruritis that disturbs sleep | Severe, constant pruritis, sleep disturbed | N/A |
| **Tinnitus*** | Mild, transient ringing or roaring sound | Moderate, persistent ringing or roaring sound | Severe ringing or roaring sound with associated hearing loss | N/A |
| **Behavioural changes** | Mild difficulty concentrating; mild confusion or agitation; activities of daily living unaffected; no treatment | Moderate confusion or agitation; some limitation of activities of daily living; minimal treatment | Severe confusion or agitation; Needs assistance for activities of daily living; therapy required | Toxic psychosis; hospitalization for treatment |
| **“Flu”**  **(viral URI)** | Mild nasal congestion, mild rhinorrhea | Moderate nasal congestion, moderate rhinorrhea | N/A | N/A |
| **Allergic reaction** | N/A | N/A | Urticaria | Severe urticaria  anaphylaxis, angioedema |
| **Convulsion** | N/A | N/A | Localized or generalized seizure | Status epilepticus |
| *** Assess only in children > 3 years of age. Answer N/A for younger children and those unable to answer.** | | | | |

Reference – Based on WHO Toxicity Grading Scale for Determining the Severity of Adverse Events

